##### Adjuvant radiotherapy

Adjuvant radiotherapy will be determined based on pathological findings. No more than 6 weeks should elapse between the date of surgery and the initiation of adjuvant therapy.

Adjuvant radiotherapy is required for the following risk factors:
ENEPositive margins or close resection margins (< 3 mm)More than 1 lymph node positive, or any lymph node > 3 cm in size on pathologyLVIpT3–4 disease

In situations where PNI alone is present, without the other risk factors above, adjuvant RT is at the discretion of the treating physicians.

Patients with positive margins or ENE will receive a 6-week course of radiation as follows:
60 Gy in 30 fractions: Area of positive margins or ENE54 Gy in 30 fractions: Operative bed, including primary tumor location and all dissected nodal levels48 Gy in 30 fractions: Undissected areas considered to be at low-risk of harbouring microscopic disease.

Patients without positive margins or ENE will receive a 5-week course of radiation as follows:
50 Gy in 25 fractions: Operative bed, including primary tumor location and all dissected nodal levels45 Gy in 25 fractions: Undissected areas considered to be at low-risk of harbouring microscopic disease.

Concurrent chemoradiation will not be delivered in the adjuvant setting unless gross tumor is left behind at the primary site or in the neck AND the patient would have received chemotherapy had they been randomized to Arm 1. Chemotherapy is NOT used for patients with ENE or positive margins. Retrospective surgical data do not support an OS benefit to the use of chemotherapy in HPV+ patients with ENE [19].

Specific radiotherapy volume definitions for Arm 2 are described in Table 3. In all cases a 5 mm CTV to PTV expansion is to be used.

**Table 3 Tab3:** Specific RT volume definition volumes for Arm 2 (Primary TOS) if adjuvant RT is required

Radiotherapy Volume		Definition
With ENE or positive margins (30 fractions over 6 weeks)	Without ENE or positive margins (25 fractions over 5 weeks)	
CTV60		Areas of positive margins and/or ENE
CTV54	CTV50	Entire tumor bed and any dissected neck nodal levels
CTV48	CTV45	Undissected nodal areas that must be treated based on pathological results. Treatment volumes must include nodal levels adjacent to areas containing involved nodes (eg. if there is a level II node positive, levels Ib and V must be included) – All patients with N1 (ipsilateral) nodal disease: ◦Ipsilateral: Ib, II-V, RP ◦Contralateral^a^: II-IV, RP only if extension to posterior pharyngeal wall or soft palate – All patients with N2 disease: ◦Ipsilateral and contralateral: Ib, II-V, RP

^a^If treating the contralateral neck

The AJCC 8th edition has a pathologically based staging system for HPV+ patients treated with primary surgery that differs significantly from the clinically based staging system used for patients treated with primary radiation. All surgically treated patients will be separately re-staged after the final pathology is available.

In the unlikely event of residual gross disease, the patient should then receive adjuvant treatment using the dose fractionations in Arm 1. In the unlikely scenario where a patient is deemed to have highly aggressive disease (e.g. frank growth/progression during the post-surgical interval), the radiation oncologist may elect to treat with a standard (non-de-escalated) dose of 70 Gy in 35 fractions. Treatment breaks, early RT termination and discontinuation of systemic therapy is at the discretion of the treating oncologist based on patient treatment toxicity.

### Unilateral vs. Bilateral radiation

Unilateral radiation is recommended if the following criteria are ALL met:
tonsil primary< 1 cm extension into the tongue base or palateno posterior pharyngeal wall extensionno ENEN0, or only a single ipsilateral lymph node positive

Unilateral radiation is optional if the following criteria are ALL met
tonsil primary< 1 cm extension into the tongue base or palateno posterior pharyngeal wall extensionno ENEmore than one ipsilateral lymph node positive, but are all less than 6 cm, and are all in level II.

In all other cases, bilateral radiation is mandatory. These criteria apply to all patients in Arm 1, and to patients in Arm 2 who require adjuvant RT. For the patients in Arm 2 who receive adjuvant RT, these criteria are based on the pathological findings and intraoperative findings, not the pre-operative clinical findings.

### Radiotherapy technique, immobilization, localization and planning

Intensity modulated radiotherapy (IMRT) will be used for all patients in this study. IMRT can be delivered using static-beam techniques or rotational techniques (e.g. Tomotherapy or Volumetric Modulated Arc Therapy [VMAT]). A custom thermoplastic shell will be used to immobilize all patients. Patients will then undergo a planning CT simulation (head and neck to below the clavicles, slice thickness 3 mm or less.) Patients in Arm 1 will receive contrast (unless contraindicated). For patients in both arms, when necessary, the planning CT will be fused with other diagnostic imaging).

Organ at risk (OAR) contouring definitions, dose constraints and planning priorities are shown in Additional file 1, adapted from RTOG protocols 1016 [20] (Arm 1) and 0920 [21] (Arm 2), HN-002 [15], ECOG-3311 [16] and the NCIC-CTG HN6 protocol [22]. Dose constraints are the same whether 25 or 30 fractions are delivered, as the radiobiological conversion factor is small.

Plans will be normalized to ensure that 95% of each PTV is covered by 100% of the prescription dose for that volume. 99% of each PTV must receive at least 93% of the prescription dose. The maximum dose must be less than 115% of the highest prescription dose.

### Quality assurance

#### Radiotherapy quality assurance

A quality assurance protocol is used to ensure safe and efficacious treatment with the following elements present for each patient:
Discussion of each radiotherapy plan at head and neck quality assurance (QA) rounds prior to, or within the first week of treatmentPhysics staff will confirm all dose delivery for IMRT plans (including arc-based treatments) before treatment.Cone-beam CT and/or orthogonal x-rays will be used daily to verify treatment positioning, as per institutional standard practice.Prior to enrolling patients, each centre will be given a sample CT dataset for contouring, planning and physics QA. Enrollment can begin once the plan and QA have been approved at the London Regional Cancer Program (LRCP).

#### Surgery quality assurance

The learning curve for surgeons carrying out transoral oropharyngeal cancer resections has been demonstrated to be short for early-stage cases, with significant improvements in operative time after 20 cases (but not oncologic outcomes) as learning occurs [23]. Surgeons will be required to complete a “Surgical Credentialing Questionnaire” based closely on the ECOG-3311 credentialing criteria (Additional file 2). This includes 1) being fellowship trained in head and neck surgical oncology, 2) having carried out at least 20 transoral oropharyngeal cancer resections as primary surgeon, 3) providing operative notes for 10 of those cases, 4) a minimum of 5 oropharyngeal resections in the last year and 5) perform at least 30 neck dissections per year.

Individual surgeons will be reviewed for surgical quality after every 5 surgical cases by the principal investigator [name]. Bleeding or positive margin rates of greater than 20% may result in exclusion from the trial at the discretion of the principal investigators. The occurrence of an oropharyngeal bleeding fatality or severe anoxic brain injury in the absence of a tracheostomy may also result in the exclusion of the centre from the trial.

Centres will be reviewed for surgical quality after 5, 10 and 15 surgical cases by the principal investigators. Bleeding or positive margin rates of greater than 20% may result in exclusion from the trial at the discretion of the principal investigators. The occurrence of an oropharyngeal bleeding fatality or severe anoxic brain injury in the absence of a tracheostomy may also result in the exclusion of the centre from the trial.

Pathology reporting of ENE: The electronic case report forms must include a description of ENE using the same descripTOS as the ECOG-3311 trial:
**absent** (node without metastasis or nodal metastasis with smooth/rounded leading edge confined to thickened capsule/pseudocapsule)**minimal** (tumor extends ≤1 mm beyond the lymph node capsule)**present - extensive** (tumor extends > 1 mm beyond the lymph node capsule (includes soft tissue metastasis))

### Subject discontinuation / withdrawal

Subjects may voluntarily discontinue participation in the study at any time. If a subject is removed from the study, the clinical and laboratory evaluations that would have been performed at the end of the study should be obtained. If a subject is removed because of an adverse event, they should remain under medical observation as long as deemed appropriate by the treating physician.

### Follow-up evaluation

Day 1 of follow-up will be the first day of radiotherapy (Arm 1) or the date of surgery (Arm 2); however, survival will be calculated from the date of randomization. The follow-up schedule is summarized in Additional file 3, and is the same as the follow-up schedule of ORATOR [24]. On Arm 1 patients will be seen during treatment, for a post-treatment clinical assessment at 4–6 weeks. Post-treatment imaging with a CT or PET/CT of the neck will be obtained. On Arm 2 a post-operative assessment will occur at 2 weeks with adjuvant radiotherapy beginning within 6 weeks of surgery if required. If radiotherapy is delivered the same treatment and post-treatment assessments will occur as on Arm 1, A return visit with the surgeon will occur at 3 months from the date of surgery. On both arms patients will be seen every 3 months up to 2 years and then every 6 months thereafter (up to 5 years) from the start of treatment, with clinical, toxicity and QOL assessments (Additional file 3). For patients in both arms, a CT of the neck, and chest, MRI of the neck with CT of the chest or whole body PET/CT will be obtained at 12 months. Additional imaging or laboratory investigations and additional treatment (eg. Salvage treatment) will be carried out at the discretion of the treating physicians.

#### Disease progression and new primary

In the event of disease progression, the details of new or recurrent disease and treatment details will be captured in the case report form. Audiologic assessments, bloodwork and QOL questionnaires should continue to be completed according to the follow up schedule (Additional file 3). All ongoing adverse events (AEs) at the time of progression should be followed until resolution. Subsequent imaging after progression can be completed at the discretion of the treating investigator.

##### Salvage surgery after primary radiotherapy

Treatment of residual disease at the site of the primary tumor will be determined by the treating physicians, and should include surgical salvage if feasible.

Management of residual enlarged lymph nodes in the neck should be guided by standard institutional practice. In general, for patients with residual enlarged nodes on CT, a PET-CT is preferred to confirm FDG avidity prior to neck dissection. If the PET-CT is negative in the setting of enlarged nodes on CT, then close interval follow-up with repeat CT every 2–3 months is recommended until the lymph nodes resolve. If PET-CT is unavailable, any nodes > 1 cm in short axis should, at a minimum, be carefully followed with repeat CT every 2–3 months until the lymph nodes resolve, with neck dissection at the discretion of the treating physician.

Salvage surgery for the primary tumor or lymph nodes within 5 months of treatment will be considered part of the initial treatment package and scored as persistent disease, not as recurrence. Surgery beyond 5 months post-treatment will be scored as recurrence if malignancy is evident in the pathology specimen.

### Measurement of outcomes

Survival outcomes:
◦ OS: time from randomization until death from any cause◦ PFS: time from randomization to either progression or death, whichever occurs first.QOL outcomes (measured at baseline and at 6-month intervals except PNQ):
◦ MDADI◦ EORTC QLQ-C30 and H&N35 scales◦ NDII◦ VHI-10◦ PNQ will be completed at 1 year post-treatment.Economic assessment:
◦ EQ-5D-5 L: administered at baseline and 6 month intervals. Quality adjusted life years (QALYs) will be assessed as the area under the preference-weighted survival curve. Overall costs of each treatment strategy will be abstracted from the available literature. The incremental cost effectiveness ratios (ICERs) between treatment arms will be compared through the standard method of ratio between differences in costs and QALYs. Point estimates for these differences can be derived from multivariable generalized estimating equations (GEE) or general linear model (GLM) analyses.Toxicity outcomes:
◦ CTC-AE toxicities will be recorded during treatment and at every follow-up visit.

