## Background

Oropharyngeal squamous cell carcinoma (OPC) is rapidly increasing in incidence, associated with rising rates of human papillomavirus (HPV) infection [1, 2]. Patients with HPV-positive (HPV+) OPC have substantially better treatment response and overall survival (OS) than patients with HPV-negative (HPV-) disease [3]. Historically the management of OPC has relied on radiotherapy (RT) based approaches as older surgical techniques required large incisions and mandibulotomies with high surgical morbidity and mortality [4]. The addition of concurrent chemotherapy to radiation improved oncological outcomes [5]. However, acute and long term side effects of RT or chemoradiation (CRT) can be severe, including frequent swallowing dysfunction, mucositis, xerostomia, fibrosis, osteoradionecrosis, neutropenia, neurotoxicity and hearing loss [6].

The introduction of minimally invasive transoral surgical techniques including transoral robotic surgery (TORS) and transoral laser microsurgery (TLM) has led to a revival of surgery as the primary treatment of OPC [7, 8]. While primary surgery with transoral surgery (TOS) can avoid some of the side effects of radiotherapy, it can have rare serious consequences such as fatal hemorrhage, stroke, shoulder dysfunction and dysphagia [9].

Currently, there is no level I evidence to favor one treatment strategy over the other. Instead, treatment selection is largely driven by institutional and patient biases with the majority of patients in the United States receiving surgery (82% of T1-T2 disease) [7], while most patients receive primary RT in Canada and Europe [10, 11].

The ORATOR trial is the only trial to examine the question of a primary RT vs. primary TOS approach in a randomized fashion [12]. This phase II trial included 68 patients with OPC regardless of HPV status, and randomized patients to RT (70 Gy, with chemotherapy if N1–2) or TOS plus neck dissection (with or without adjuvant RT/CRT, based on pathology). The primary endpoint was swallowing-related quality of life (QOL) at 1 year, measured using the MD Anderson Dysphagia Inventory (MDADI) [13]. The study found that at 1 year there was a statistically significant difference in swallowing QOL but that this difference did not represent a clinically meaningful change (less than a 10-point difference).

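### Two sections disagree on how often QOL is measured; on the 6-monthly version, the QALY area omits any acute utility loss that has resolved by month 6

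*Protocol article*

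**What the plan says.** Measurement of outcomes sets the QOL timetable as "QOL outcomes (measured at baseline and at 6-month intervals except PNQ"). The exception is explicit: "PNQ will be completed at 1 year post-treatment". Under the economic assessment it adds "EQ-5D-5 L: administered at baseline and 6 month intervals" and then "Quality adjusted life years (QALYs) will be assessed as the area under the preference-weighted survival curve". These QALYs form the denominator of the planned ICERs.

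Follow-up evaluation reads differently: "On both arms patients will be seen every 3 months up to 2 years", with 6-monthly visits after that up to 5 years, counted "from the start of treatment, with clinical, toxicity and QOL assessments (Additional file 3"). It does not say that QOL is taken only at alternate visits. It refers the reader to Additional file 3 for the detail and says that the schedule is the one used in ORATOR.

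Toxicity is handled separately. Measurement of outcomes has CTC-AE recorded throughout treatment and at each follow-up visit.

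**The concern.** Surgery, radiotherapy, chemotherapy and adjuvant radiotherapy all fall early in the first half-year. If EQ-5D-5L is taken at baseline and next at month 6, the area between those points is a straight line. A patient whose utility falls during treatment and recovers by month 6 contributes no loss at all.

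The Background section warns that "acute and long term side effects of RT or chemoradiation (CRT) can be severe", and the abstract says that the two approaches differ in their spectrum of toxicity. If acute losses differ between arms, leaving them out favours the arm with the deeper one. It also shifts the ICER, whose denominator may be small. The early part of the QOL-profile comparison, which is one of the stated objectives, would be missing too. A later analysis plan cannot repair this, because utilities that were never collected cannot be recovered.

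**Working it through.** The protocol gives no QALY figure or utility, so there is nothing of its own to reproduce. The check has three steps: the treatment timeline, the area missed, and what a month-3 reading would recover.

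**1. Timeline.** Follow-up day 1 is the first day of radiotherapy (Arm 1) or the date of surgery (Arm 2), from Follow-up evaluation.
- Arm 1: radiotherapy lasts 5 or 6 weeks (Table 1), so treatment ends at week 5 to 6.
- Arm 2 with adjuvant radiotherapy: up to 6 weeks from surgery, then 5 or 6 weeks (Adjuvant radiotherapy), so 6 + 5 = 11 to 6 + 6 = 12 weeks.
- The first QOL point on the 6-monthly text is about week 26, if counted from the start of treatment. That is 26 − 6 = 20 to 26 − 5 = 21 weeks after Arm 1 treatment ends, and 26 − 12 = 14 to 26 − 11 = 15 weeks after the latest Arm 2 adjuvant course ends.

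Salvage surgery and the exceptional non-de-escalated course in Arm 2 are left out of this timeline.

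**2. Area missed (assumed utilities).** Take a triangular dip that starts at treatment, is deepest (d) at 1.5 months and has gone by month e. The true loss in QALYs is ½ × d × e/12 = d × e/24. With readings at 0 and 6 months only, both equal the baseline value and the recorded loss is 0. With readings at 0, 3 and 6 months, the month-3 value is d × (e − 3)/(e − 1.5) below baseline, and the trapezoid area is 0.25 × that value.

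| d | e (months) | True loss | 0 and 6 months | 0, 3 and 6 months |
|---|---|---|---|---|
| 0.05 | 4.5 | 0.0094 | 0 | 0.0063 |
| 0.10 | 6 | 0.0250 | 0 | 0.0167 |
| 0.20 | 6 | 0.0500 | 0 | 0.0333 |
| 0.30 | 6 | 0.0750 | 0 | 0.0500 |

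The missed loss per arm is thus about 0.01 to 0.075 QALY. For this shape a month-3 reading recovers two thirds of it (for example 0.0500/0.0750).

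The bias in the comparison is the missed loss in one arm minus that in the other. With equal dips it is 0. With depths of 0.20 and 0.10, both gone by month 6, it is 0.0500 − 0.0250 = 0.0250. At the extremes of the assumed range it is 0.0750 − 0.0094 = 0.0656.

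**3. Limit of a month-3 reading.** The arms finish treatment at different times. Suppose both have a dip of depth d that is gone by week 26, deepest at week 6 in Arm 1 and week 12 in Arm 2. The true loss is ½ × 0.5 × d = 0.25d in each arm.
- Arm 1 at week 13: d × (26 − 13)/(26 − 6) = 0.65d, area 0.25 × 0.65d ≈ 0.16d.
- Arm 2 at week 13: d × (26 − 13)/(26 − 12) ≈ 0.93d, area 0.25 × 0.93d ≈ 0.23d.

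The 3-month schedule then shows a spurious difference of about 0.07d, or 0.017 QALY at d = 0.25. Baseline and month 6 alone would show none.

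**The case against.** The strongest reply is that the gap may not exist. If Follow-up evaluation governs, QOL is already taken at month 3. If Measurement of outcomes governs with QOL at alternate visits, the plan has simply chosen a schedule, and one shared with ORATOR, against which a QOL comparison is planned. Additional file 3 would decide between these. This stands as far as it goes: the firm point is that the two sections do not clearly agree, and the QALY consequence is conditional on the 6-monthly text. Adding a reading would not prevent the comparison with ORATOR at the shared time points.

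Three stronger readings are tempting, and the documents do not support them.
- A reader might infer that the acute toxicity period is skipped. It is not, because CTC-AE covers treatment and every visit. Those grades do not, however, supply the preference weights that a QALY needs.
- A reader might infer that the arms are expected to differ mainly in the early months. The protocol says only that toxicity spectrums differ. It rests its QOL rationale on long-term sequelae and sets the named MDADI endpoint and the t-test at 1 year, which either schedule covers. That the arms may differ early is an inference from their different treatments.
- A reader might take the missed loss per patient as the error in the QALY difference, or call it a given share of the true difference. Only the between-arm difference in missed loss matters, and the documents give neither utilities nor an expected QALY difference.

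The timing objection in step 3 is arithmetically right. It shows that one added point is an incomplete correction, not that recording no acute utility is sounder.

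**Conclusion.** The concern holds in a limited, conditional form. Measurement of outcomes and Follow-up evaluation give QOL timetables that do not clearly agree and must be reconciled. On the 6-monthly text, the QALY area omits acute loss that has resolved by month 6. The QALY difference and ICER are biased if that loss differs between arms, in favour of the arm that loses more.

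The size is unknown. The range in the working rests on assumed depths and on a triangular shape with recovery by 4.5 to 6 months. The effect is confined to the economic assessment and the early QOL profile. QALYs and ICERs are not among the listed secondary endpoints, where EQ-5D-5L appears only as one of the QOL scales. OS, PFS, toxicity recording and the 1-year MDADI comparison are untouched. This is a cheap improvement and does not threaten the trial's main conclusions.

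**What to change.** State one QOL schedule, in the same terms, in Measurement of outcomes and Follow-up evaluation, and check it against Additional file 3. Include EQ-5D-5L at the existing 3-month visit, preferably with MDADI and QLQ-C30/H&N35, and use the month-3 values in the QALY area and the mixed models. If Additional file 3 already provides for this, only Measurement of outcomes needs correcting.

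The cost is one extra questionnaire administration at a visit that is already scheduled. The remaining weakness is that month 3 falls 13 − 6 = 7 to 13 − 5 = 8 weeks after Arm 1 treatment ends but only 13 − 12 = 1 to 13 − 11 = 2 weeks after the latest Arm 2 adjuvant course. A single reading therefore captures the dip partly and unequally. State this as a limitation, or vary the assumed shape between readings in a sensitivity analysis of the QALY difference.

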### Statistical considerations

#### Randomization

Patients will be randomized between Arm 1: Arm 2 stratified based on smoking status (< 10 pack-years vs. ≥10 years) in a 1:1 ratio in a permutated block design. The randomization sequence is known only to the statistician and uploaded into a restricted-access database (REDCap) housed on secure hospital servers at LHSC [25]. Upon enrollment of a patient, the database will be accessed by the trial coordinator to obtain the next intervention in the random sequence, for the pertinent stratum, which will then be assigned to the patient.

